## Qualitative Component

### **In-depth Interviews**

We will conduct qualitative in-depth interviews with a subset of up to 65 participants from Phase 3 of the study. Each woman will be interviewed one time. Interviews will be conducted by a trained isiXhosa-speaking research assistant using an interview guide in order to examine experiences including: study participation; ART initiation during pregnancy generally; post-partum follow-up on ART; and transitions to routine adult ART services. Qualitative interview participants will be selected purposively, to include women who are approximately 6-9 months post-partum. All participants will sign a separate informed consent form for this component of the study.

### **Clinic observation**

Clinic observation in this study will consist of approximately five half-day sessions in the ART clinic within the MOU as well as the general adult ART clinic at Hannan Crusad and potentially another ART clinic location (to be identified), and will be conducted by the primary qualitative researcher, as well as one fieldworker. During clinic observation, the researchers will record extensive notes in the form of field notes, about the clinic environment. Informal conversations with both patients and staff will be recorded collectively. Field notes by both the primary qualitative researcher, as well as the field worker, will be read and discussed.

### Cost-effectiveness

Costing data will be used alongside findings on clinical outcomes in order to understand the cost-effectiveness of the two strategies for ART services during the postpartum period. Data on unit costs, including human resources costs, will be abstracted from routine facility accounts, facility utilization data and staffing plans, and pharmacy accounts maintained by the PGWC; data on service utilization by participants will come directly from the study data; program costs will be based on local standards for training and materials development; overhead costs will be based on PGWC accounts.

### Identification of health care needs during study procedures

At every study measurement visit, any woman found to have an unmet health need (whether medical, obstetric, postpartum family planning, or related to mental health or substance use) will be referred to the relevant service within the Gugulethu CHC or higher levels of care, as appropriate. In particular:

- Any woman found to have defaulted ART during any Phase of the study will be re-referred to the relevant ART service (general adult or MCH-focused) via the Gugulethu MOU.
- Any woman found to be non-adherent to ART at any study measurement visit will receive intensive counselling on ART use, and referred to the relevant ART service for follow-up.
- Any woman found to be experiencing domestic or partner violence in any form will be referred to the main local NGO supporting victims of domestic violence (MOSAIC) and the South African Police Service (per the Domestic Violence Act, No. 116 of 1998) with follow-up to ensure adequate attention.

- Any child found to be HIV-infected will be referred immediately to the nearest paediatric ART service for assessment and infant ART initiation.
- If any infant health care needs identified, the infant will be referred to the appropriate paediatric health services via the Gugulethu Community Health Centre.

### Staff training

Prior to initiation of the study, all staff that will have contact with participants will take part in a multi-day study-specific training. The curriculum of the training will include: rationale, purpose, and scientific objectives of the study; study design and methodology; conduct of study assessments, tracking of participants, completion of study forms, and data collection; staff responsibilities; recruiting participants; procedures for enrolling participants into the study; randomization, universal precautions, communication skills, safety in the field, ethical guidelines for research including participants' rights; procedures for obtaining informed consent; and confidentiality requirements.

Study staff will receive a hands-on training that will include an introduction to data collection forms and procedures. Mock interviews will be an essential component of the training and protocol team members will act as both the trainer and the mock respondent. The trainer will take the staff through each step of the data collection process, from enrolling participants to ending the study visit and completing any necessary forms. Study staff will be given a chance to practice both the English and isiXhosa versions of all the assessments in order to discuss and resolve any issues. Training for study staff is expected to take approximately 1 week and additional follow-up training, as necessary.

Study staff members who will collect blood samples and conduct laboratory analyses will receive training in universal precautions, sample collection, and testing of study samples.

In addition, staff will be trained in the management of crisis situations, including reports of abuse and domestic violence, that may be disclosed during study participation. The site will have established procedures for managing these situations and procedures in place for providing counselling and appropriate referrals. Procedures for managing these issues will be outlined in study SOPs.

For all study staff, there will be additional training days scheduled during the study for refresher training. During these refresher trainings, study staff will review study procedures and discuss any challenges encountered. All staff who through the course of their work have knowledge of, or access to, personal information about participants will be required to complete training on patient confidentiality and sign a confidentiality agreement before the start of data collection.

### Contamination and masking

Contamination between groups is a concern and blinding participants to this type of health systems evaluation is not possible. Contamination would mean that women in the general adult ART group may be aware of the MCH-focused ART group, or vice-versa, and change their behaviours related to their own ART use, retention in care, and/or infant feeding practices. Detection biases are possible for self reported outcomes due to lack of blinding, but one of the primary outcomes (HIV viral load) is objective. Insofar as possible, we will mask study

personnel involved in the study measurement visits. In addition, we will conduct the study measurement visits from a space at the Gugulethu CHC that is separate from both the general adult ART services and the MCH-focused ART services, with study staff who are different from participants' service provider, in order to minimize possible biases in assessment.

## **9. Participant Retention**

At enrolment into Phase 1, all women will be asked to provide detailed locator information. Specifically, participants will be asked to provide the following information: full name, address, contact numbers (including landline and cellphone) and the names, addresses, and contact details for two individuals who the participant lives with and one alternate individual who the participant does not live with. At later visits, participants will be asked to update their contact information if needed. All locator information is kept in locked study cabinets accessible only under the direction of the study coordinator.

After enrolment, all study activities will take place through appointments conducted separately from ANC and ART care. There will be two main approaches to tracing participants who miss study appointments:

- Telephonic contact is made with the participant or with an alternate individual pre-designated by the participant.
- If telephone attempts fail, study fieldworkers visit the home address of the participant to trace the participant in person.

All participant tracing efforts by any staff (via phone or home visit) will not mention the reason for the contact, or anything regarding HIV/AIDS or ART. All contacts simply request that the participant come to the clinic the next working day for a health-related issue. Our research team has been working in this setting for more than 8 years, has close knowledge of the local community, and has extensive experience with retention activities around HIV/AIDS.

As part of research activities, we will include an assessment of whether the participant is taking ART. For those women found to be not using ART, staff will facilitate an urgent referral back to the appropriate services per randomization assignment. Details and examples of these retention procedures, including this adherence assessment, will be included in the staff training to be conducted prior to study implementation.

### **Participant withdrawal**

All participants may refuse or voluntarily withdraw from the study for any reason and at any time. As part of the informed consent process, staff will state specifically that participation in the study is voluntary and that a participant may refuse participation or withdraw from study participation at any time. Participants will be told that withdrawal from the study will have no effect on their access to health facilities providing antenatal care or HIV-related testing, care and treatment services. All study staff will be trained to ensure that participants have a firm understanding of this concept at the time of the informed consent process; per consenting requirements, the informed consent form will also include a statement to this effect.

## **10. Analytic considerations**

The study is a multiphase evaluation, with the main component designed to compare the impact of two different ART management strategies on clinical, behavioural, acceptability and cost-effectiveness outcomes among HIV- positive ART-eligible pregnant women seeking antenatal care. The primary outcomes, to be assessed using a randomised trial design (Phase 3), are viral suppression and retention in care of mother and infant at 12 months postpartum. The study analysis is driven by two competing hypotheses:

- **Hypothesis 1:** Maintaining women in MCH-focused ART services during the postpartum period will result in a higher proportion of women retained in care and virally suppressed throughout the period of infant HIV exposure via breastfeeding, compared to referral of women to general adult ART services early postpartum.
- **Hypothesis 2:** Referral of women to general adult ART services earlier in the postpartum period will result in higher levels of retention on ART at 12 months postpartum, compared to maintaining women in MCH-focused ART services throughout the breastfeeding period.

### **Sample size considerations**

The sample size calculations are based on the following assumptions:

- A superiority comparison between the MCH-focused ART services group and the general adult ART services group using 90% power ( $\beta=0.1$ ) and a two-sided  $\alpha=0.05$ .
- 1:1 randomization to general adult ART services (Arm A) and MCH-focused ART services (Arm B)
- An expected proportion of women not retained in care and/or not virally suppressed at 12 months postpartum of 25% in the general adult ART services group (denoted  $\pi_C$ ), with this parameter ranging from 20-30% in different scenarios.
- The proportion of women retained in care and virally suppressed at 12 months postpartum in the MCH-focused ART services group (denoted  $\pi_I$ ) is expected to be 10%.
- Thus, the expected minimum difference in the combined endpoint of retained in care and virally suppressed between the MCH-focused and general adult ART strategies is 15% (i.e.  $\pi_I - \pi_C \geq 0.15$ ). This absolute difference corresponds to risk ratio of approximately 0.4.

*Estimated sample sizes required under different assumptions*

| Proportion of women retained in care and VS at 12m postpartum in MCH group | Absolute increase in outcome, control minus intervention | Proportion of women retained in care and VS at 12m in general ART group | Sample size required (total) |
|----------------------------------------------------------------------------|----------------------------------------------------------|-------------------------------------------------------------------------|------------------------------|
| 0.1                                                                        | 0.1                                                      | 0.2                                                                     | 572                          |
| 0.15                                                                       | 0.1                                                      | 0.25                                                                    | 708                          |
| 0.2                                                                        | 0.1                                                      | 0.3                                                                     | 824                          |
| 0.1                                                                 | 0.15                                              | 0.25                                                             | 292                   |
| 0.15                                                                       | 0.15                                                     | 0.3                                                                     | 348                          |
| 0.2                                                                        | 0.15                                                     | 0.35                                                                    | 396                          |
| 0.1                                                                        | 0.2                                                      | 0.3                                                                     | 184                          |
| 0.15                                                                       | 0.2                                                      | 0.35                                                                    | 214                          |
| 0.2                                                                        | 0.2                                                      | 0.4                                                                     | 238                          |

This sample size has been adjusted to account for anticipated loss to follow-up before the primary outcome can be assessed at 12 months postpartum. We originally expected a maximum of 20% loss to follow up, however as the study has progressed we are experiencing higher rates of loss than originally projected. Accounting for this, we anticipate that up to 390 women need to be enrolled into Phase 3 of the study, with approximately 195 randomized to each study group.

Note that from July 1 2013, local PMTCT guidelines shifted to recommend initiation of triple-drug ART for all HIV-infected pregnant women regardless of CD4 cell count. This policy shift has significant implications for interpretation of the study results, as participants enrolled before July 1 2013 (with ART eligibility based on CD4 cell count <350 cells/ $\mu$ l) represent a relatively morbid subset of the total population of pregnant women who are eligible for ART under the new guidelines. To ensure operational relevance of the study towards local policy and services, we plan to recruit the above mentioned sample size (n=390) in women initiating ART under the new policy (after 1 July 2013). Participants enrolled before this time (approximately 300 participants in Phase 1, 100 participants in Phase 2, and 90 participants in Phase 3) will be treated as a separate study population to be included in secondary analyses. Thus for the total study period, we anticipate up to 480 women enrolled into Phase 3.

In order to enrol up to 480 women into Phase 3, we anticipate enrolling a maximum of 600 women in Phase 2, and a maximum of 1600 women into Phase 1.

#### Data management

Data management will take place at the site following procedures established for multiple previous studies conducted in Gugulethu. Data collected on paper forms will be entered into a custom designed Microsoft Access database, maintained in a firewall-protected UCT server with nightly backups. The study database will be password-protected following standard password safety procedures. The database will be designed and maintained by a senior data manager who will develop the data dictionary, direct queries, and data quality assurance / quality control activities, and will supervise the data entry clerk. Data quality assurance will be in the form of robust database structure and platform, “front-end” data checks, including real-time database queries. Quality control will be through data checking scripts to identify out-of-range values, logic violations, and missing observations. Data editing will be based on reference to the form and/or source document in question; all data queries and responses will be logged, and edits will be implemented through separate program files. All study records will contain anonymous participant identification numbers, and no participant names or identifiers will be recorded.

Qualitative data from in-depth interviews will be translated and transcribed without participant names. All electronic files will be encrypted and password protected.

#### Data analysis

Data will be exported to Stata Version 12.0 (Stata Corporation, College Station, Texas) or R (Gnu Project) for analysis. All analyses will be carried out under supervision by the study statistician. All outcomes will be blinded to investigators until the data are cleaned and data analyses completed.

As described above, the primary analysis population (up to n=390) is all women enrolled into Phase 3 of the study who initiated ART during pregnancy after 1 July 2013 when the new provincial PMTCT guidelines were implemented. The subset of women in Phase 3 who initiated ART before this time (n=90, approximately) will contribute to a secondary analysis population comprised all women initiating ART in pregnancy and enrolled into Phase 3 during the study period (up to n=480).

For the primary objective, we hypothesize that women in the MCH-focused ART group will be more likely to be retained in care (defined as attending ART clinical appointments and/or medication refill visits in the window between 9 and 12 months postpartum) and maintain viral suppression (defined as <50 copies/mL, with secondary analyses at other thresholds) at 12 months postpartum, compared to women randomized to the general adult ART group. Comparisons of study groups at enrolment will be stratified by duration of ART during antenatal period (i.e., prior to randomization), and will examine demographic and HIV-related variables. Comparison of outcomes will be based on Fisher's exact test, comparing the proportion of women in each arm reaching the primary endpoint and its components; all statistical tests for the primary analysis will be two-sided at  $\alpha=0.05$ . Analyses will be by intention-to-treat, with secondary analyses stratified by duration of postnatal follow-up in the MCH-ART arm. The duration of viral suppression during the postpartum period will be defined as cumulative study time with a documented VL<50 copies/mL (with sub-analyses for <400 and <1000 copies/mL). Kaplan-Meier methods stratified by study group will be used to describe time to detectable viraemia and time to defaulting care, with proportional hazards models used to examine the independent influence of participant characteristics. Note that primary analyses will draw only on women enrolled into Phase 1 and initiating ART after 1 July 2013; women initiating ART before this time will be included as a secondary analysis population for selected analyses.

To address secondary objectives 2.1 and 2.2, data analysis of routinely collected measures of participants' use of PMTCT and ART services collected as part of Phases 1 and 2 will focus on the description of proportions of women receiving specific PMTCT services, and the delays calculated between various steps in the PMTCT cascade, including CD4 enumeration, return of CD4 results to patients and referral for ART, and initiation of ART. These analyses will employ proportions with exact 95% confidence intervals, and median delays (in days) with interquartile ranges. We will compare the proportions of women completing steps in the ART cascade, and the delays to specific steps, by basic demographic, psychosocial and clinical characteristics, collected during Phases 1 and 2. Comparisons will employ exact tests or rank-sum tests, as appropriate; statistical tests will be 2-sided at  $\alpha=0.05$ .

To address secondary objective 2.3, we will compare the two strategies for delivering ART during the postpartum period within subgroups of patients based on demographic, clinical and psychosocial characteristics measured antenatally (during Phase 2) and/or postnatally (during Phase 3). *A priori* subgroups will include:

- *Demographic characteristics* (age; gravidity/parity; education)
- *Clinical history & characteristics* (timing of HIV diagnosis; prior PMTCT or ART exposure)

- *Psychosocial characteristics* (measures of mental health and substance abuse; HIV- and ART-related knowledge and beliefs; adherence self-efficacy; perceived social support; disclosure of HIV status and ART use)
- *Antenatal ART use* (including duration of ART before delivery; adherence to ART during antenatal period)

Note that we will not adjust  $\alpha$  for multiplicity but will name these as *a priori* subgroup analyses that are secondary to the primary comparison of interest (in the overall intention-to-treat population).

Secondary objective 2.4 will be addressed through analyses of the association between demographic, psychosocial and clinical measures (including characteristics of antenatal ART use) on the primary outcome. Analyses will parallel the pure count and time-to-event methods described for the primary objective. In addition, we will use proportional hazards models to identify measures independently associated with the primary outcome and its constituents; variable selection will be based on directed acyclic graphs developed *a priori* to help distinguish causal intermediates from confounding variables (for instance, antenatal ART adherence may be a causal intermediate through which demographic or psychosocial characteristics influence the primary outcome, rather than a confounder). All regression analyses will include trial arm as a covariate; other aspects of model building and diagnostics will follow standard approaches. Outputs will be expressed as hazard ratios and 95% confidence intervals.

Comparison of secondary outcomes between the two postnatal ART services will employ both pure count and person-time methods, as described above. Patterns of women's missed visits during the postpartum period (objective 2.5.A) will be analysed according to the frequency of different numbers of missed/late visits, and the timing of the missed/late visits during the postpartum. Breastfeeding practices (objective 2.5.B) will be analysed according to the duration of exclusive breastfeeding from birth; the duration of mixed feeding; and the timing of final infant exposure to breastmilk. Maternal viral suppression (objective 2.5.C) will be analysed according to the frequency and timing of detectable viraemia (with cutpoints at <50 and <1000 copies/mL) as well as 'survival' to detectable viraemia through 12 months. Incidence of infant respiratory and/or diarrhoeal illness (objective 2.5.D) will be analysed using person-time methods; comparisons of infant growth parameters will use dependent (intra-child) and independent (between child) comparisons. Rates of mother-to-child transmission will be compared at 6 weeks and 12 months using pure count methods (objective 2.5.E).

The BSID-III developmental scores by subscale, using raw, composite and percentile scores, will address objective 2.6. Developmental delay will be classified as more than 1 standard deviation from mean. Although the BSID-III normative scores are based on United States-based populations, similar scores were observed in a South African population, in a similar setting to ours. Based on consultation with paediatric developmental specialists in our area, a difference in mean score of >5 will be used to define a clinically significant difference between subgroups. The primary exposure variable will be maternal HIV disease severity during pregnancy, as measured by clinical, immunological and virological measures at booking and delivery. Third variables will be identified *a priori* via directed acyclic graphs; these will include baseline, cumulative and time-varying measures (including maternal mental health, antenatal alcohol

and/or substance abuse, food insecurity, household asset index, gestational age, birth weight and subsequent infant growth). Throughout, units of analysis will be mother-infant pairs, with maternal and infant exposures as predictors of infant neurodevelopment. The distributional attributes of the BSID-III scores will determine the final generalized linear models of choice. A mixed effects model will be utilized to allow for repeated exposure measures and missing data.

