### Key issues in optimizing ART for maternal and child health

The proposed research is based on recent developments in our understanding of both PMTCT and the delivery of ART services.

*Viral suppression drives MTCT transmission risk during pregnancy and postpartum.* Most MTCT takes place in ART-eligible women who have the highest pre-ART viral loads: among HIV-infected pregnant women in Zambia, 77% of MTCT during the perinatal period as well as 83% of transmission in the postnatal period took place in ART-eligible women with CD4 cell counts <350 cells/ $\mu$ L [20]. Maternal viraemia is the critical determinant of MTCT *in utero*, intrapartum and postpartum, and the primary effect of antiretrovirals on MTCT is through reducing maternal viral load. Viral suppression at delivery and during the postpartum period is a direct function of pre-ART viral load and duration of ART [21]. There is good evidence from South Africa showing that increasing duration of ART in pregnancy is strongly associated with reduced infant transmission [22], with MTCT rates of 9.3%, 5.5% and 3.5% observed in ART-eligible women on ART for <4 weeks, 4-16 weeks, and > 16 weeks, respectively [11]. Other research has demonstrated that the benefits of early ART initiation extend to the postpartum when infants continue to be exposed to maternal HIV through breastfeeding [23].

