### **Phase 2**

Participants who are eligible for ART according to current local recommendations for ART eligibility, and who meet other eligibility criteria outlined in Section 4, will be invited to participate in Phase 2 of the study at the end of their second antenatal clinic visit. As part of this, women completing informed consent #2 will complete three study measurement visits: on the same day (i.e., after the second antenatal clinic visit, *study visit 2*), during the late third trimester (*study visit 3*; scheduled based on gestation at enrolment into Phase 2 to be approximately 32-36 weeks' gestation), and within 7 days postpartum (*study visit 4*; timed to coincide with the routine postnatal clinic visit held 2-4 days postpartum). These study measurement visits will last 30-45 minutes each. At these visits:

- *Antenatal study visits.* Questionnaires will be administered on recent pregnancy- and HIV-related health care, HIV disclosure, and ART use (including side effects and adherence). At selected antenatal visits, additional instruments will collect data on HIV treatment knowledge, beliefs about ART medications, stigmatization, social support, experiences of partner violence, and mental health measures.
- *Postpartum study visit.* Questionnaires will be administered on antenatal, obstetric and HIV-related health care, HIV disclosure, and ART use (including side effects and adherence). Additional instruments will collect data on obstetric information, family planning, quality of HIV care during pregnancy, infant feeding practices, and infant health and health care (including adherence to daily nevirapine prophylaxis).

- At each study visit, participants will undergo phlebotomy to draw 5mL of venous blood for storage and batched viral load testing.

### Phase 3

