### *Randomization*

Randomization will take place at the end of the study measurement visit within the first week postpartum. Randomization will follow a dynamic permuted block design. Randomization numbers will be generated prior to the start of the study, and placed in sequentially numbered opaque envelopes. Randomization envelopes will be stored in a locked cabinet in the study office at UCT that will be accessed by the study coordinator when a woman is fully consented and has completed the immediate postpartum study visit, with independent documentation of the participant ID number, randomization date, and randomization assignment. The study coordinator will provide the MOU-ART service with a regularly updated list of women to be retained within the MOU-ART service until they have ended breastfeeding. The study coordinator involved in randomization will not be involved in interviewing participants.

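### The primary comparison is an unadjusted Fisher's exact test, which leaves prognostic viral load and ART duration, fixed before randomisation, unused: a loss of efficiency, not of validity

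*Protocol*

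**What the plan says.** The Data analysis section compares outcomes by Fisher's "exact test, comparing the proportion of women in each arm reaching the primary endpoint" and its components. It adds that "all statistical tests for the primary analysis will be two-sided" at 0.05, and that analysis is by intention to treat. No covariate or stratum is named for this comparison.

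The Background, under key issues in optimising ART, states: "Viral suppression at delivery and during the postpartum period is a direct function of pre-ART viral load and duration of ART".

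Both quantities are available and are fixed before allocation:
- Section 8, Phase 1 takes blood for viral load at the first antenatal visit. For women who start ART in this pregnancy, that is the pre-ART value.
- At each Phase 2 visit, including visit 4 within a week of birth, "participants will undergo phlebotomy to draw 5mL of venous blood for storage and batched viral load testing".
- The date of ART initiation is abstracted from clinical records.

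Randomisation takes place at the end of visit 4. The protocol says "Randomization will follow a dynamic permuted block design" and names no stratification factor. The Phase 3 inclusion criteria require ART started antenatally and current breastfeeding, but neither viral suppression nor a minimum time on ART.

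Antenatal ART duration is used in three other places: to stratify the comparison of arms at enrolment, as an a priori subgroup, and as a predictor under secondary objective 2.4.

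**The concern.** Women will enter Phase 3 with very different lengths of ART and, probably, different degrees of viraemia. If these carry forward to the 12-month endpoint, an unadjusted comparison leaves explainable variation in the error term. It also lets any chance imbalance between arms pass into the primary result. The protocol already pays for the measurements that would remove part of this, and it treats ART duration as important everywhere except in the primary test.

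Fisher's test also has an actual size below its nominal 5%, which costs further power. What is at stake is precision, mainly if the true effect is smaller than the 15 points planned for.

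**Working it through.** **1. Reproduce the planned size.** Inputs from Sample size considerations: "A superiority comparison between the MCH-focused ART services group and the general adult ART services group using 90% power", two-sided 0.05, 1:1 allocation, and an expected proportion not retained and/or "not virally suppressed at 12 months postpartum of 25% in the general adult ART services group". The 10% for the MCH arm is labelled as success there, but it fits the stated risk ratio of about 0.4 only as a failure proportion, and I use it so.

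- Uncorrected: n = [1.960 × √(2 × 0.175 × 0.825) + 1.282 × √(0.10 × 0.90 + 0.25 × 0.75)]² / 0.15² = 132.8, so 133 per arm (266 in total).
- Continuity-corrected: n′ = (n/4) × [1 + √(1 + 4/(n × 0.15))]² = 145.8, so 146 per arm, or 292. This is the protocol's figure.
- 292 / 0.75 = 389.3, so 390 enrolled implies about 25% loss.

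**2. Fisher's test by exact enumeration.**

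| Failure rates | Per arm | Rejection probability |
|---|---|---|
| 10% v 25% | 146 | 90.9% |
| 10% v 25% | 195 | 97.1% |
| 15% v 25% | 146 | 51.9% |
| 15% v 25% | 195 | 65.7% |
| 25% v 25% (size) | 146 | 3.6% |
| 17.5% v 17.5% (size) | 146 | 3.5% |

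The continuity-corrected size already pays for the conservatism at the design effect.

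**3. Information gained by adjusting for visit-4 suppression.** The protocol gives no association between baseline viral load and the endpoint, so everything in this step is an assumption. Let s be the share suppressed at visit 4 (60-80%) and g the gap in control-arm failure between women not suppressed and women suppressed. Overall failure is held at 25% and 10%, with the risk ratio of 0.4 in both strata, so the MCH-arm gap is 0.4g.

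- Unadjusted variance (times n per arm): 0.25 × 0.75 + 0.10 × 0.90 = 0.2775.
- Net reduction from standardising over strata: s(1−s)(g + 0.4g)²/2 = 0.98 × s(1−s) × g².
- Gain = 0.2775 / (0.2775 − reduction) − 1.

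| g | s = 80% | s = 60% |
|---|---|---|
| 10 points | reduction 0.0016, gain 0.6% | 0.0024, 0.9% |
| 20 points | 0.0063, 2.3% | 0.0094, 3.5% |
| 30 points | 0.0141, 5.4% | 0.0212, 8.3% |
| 50 points | 0.0392, 16% | 0.0588, 27% |

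So the gain is about 1-4% for gaps of 10-20 points and about 5-27% for gaps of 30-50 points.

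On the same assumptions, a chance imbalance of 10 points in visit-4 suppression shifts the unadjusted risk difference by 0.10 × (g + 0.4g)/2 = 0.07g. That is 0.7 points at g = 10 and 3.5 points at g = 50.

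**4. Power with a continuous covariate, by simulation** (2,000 trials per cell; assumed log odds ratio per SD of 0.5 to 2.0; 146 per arm).

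| Failure rates | Fisher | Unadjusted chi-square | Adjusted logistic |
|---|---|---|---|
| 10% v 25% | 91-92% | 93-94% | 94-98% |
| 15% v 25% | 51-53% | 56-58% | 59-75% |

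With 195 per arm and 15% v 25%, Fisher's test gave 64-67% and the adjusted test 71-85%. Type I error of the adjusted test at 146 per arm was 4.2-5.8%. At the weak end of the range, most of the gain comes from leaving Fisher's conservatism rather than from the covariate.

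**The case against.** The strongest reply is that nothing is broken. Fisher's test is valid under randomisation, the sample size was computed with the matching continuity correction, and the stated 90% power is reached. This stands. A reader might infer from the conservatism that the trial is underpowered for its own design effect; step 2 shows that it is not.

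A second reply is that the protocol does not call visit-4 viral load a determinant of suppression. This also stands: the Background names the pre-ART value and duration of ART. Visit-4 viral load has to be justified on its own merits, as the latest value of the outcome variable drawn before allocation. Later batch testing does not change that status.

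Third, the association may be weak. The endpoint combines retention with suppression, and the Background calls failure to retain patients the most widespread form of non-adherence. A woman viraemic at delivery only because she started late has a further year of ART before the endpoint. This is a fair reason not to assume a large gain, and why the range must include about 1%.

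Fourth, ART duration stratifies the enrolment comparison, and objective 2.4 plans regression models that include trial arm, with 95% CIs. These make an imbalance visible and give adjusted arm estimates, but the models are secondary and on the hazard scale. They do not supply an adjusted difference in 12-month proportions.

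Last, a statistical analysis plan not shown could add an adjusted estimate or a confidence interval for the difference. The protocol excludes neither, so their absence is no error. The choice of the unadjusted test as the basis of the comparison is nevertheless stated in the protocol itself.

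**Conclusion.** The point holds as one of efficiency. The protocol fixes an unadjusted primary test while holding, for every randomised woman, values fixed before allocation that it considers prognostic or that measure the outcome variable directly.

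At the planned 10% versus 25% the practical loss is small, because power is already 90.9% with 146 per arm. It could matter at 15% versus 25%, where Fisher's test has about 52% power and adjustment gave 59-75% over the assumed range.

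A reader might infer that adjustment is certain to be worth dozens of women. The protocol does not support that: the gain is about 1-4% in information for modest associations and reaches 5-27% only if failure differs by 30-50 points by visit-4 suppression. Nor does it support reading the planned test as invalid. The conclusion rests on the assumed association, on 60-80% suppressed at visit 4, and on the failure-rate reading of the sample size table. The change is worth making because it costs so little.

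**What to change.** Before outcomes are unblinded, prespecify as the primary analysis the risk difference, with the risk ratio, and 95% confidence intervals from a logistic model standardised over both arms. Adjust for:
- log10 viral load before randomisation (the visit-4 value, the visit-1 pre-ART value, or both, with the choice stated in advance);
- weeks of ART before delivery.

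Handle missing covariate values with a missing-indicator, so that no randomised woman is dropped for lack of a baseline value. Keep Fisher's exact test as the unadjusted sensitivity analysis. Endpoint, population and sample size stay as they are.

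The cost is a wording change, slightly more analysis work, and linkage of the batched viral loads and ART start dates to the randomised women. No new visits, samples or participants are needed.
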